### Remuneration

Participants receive a US $25 e-gift card after completing each survey at baseline, 3 months, 6 months, and 12 months, along with a US $25 bonus for completing all surveys, for a total of US $125. Payments are sent via an e-gift card to the participant’s email after each survey is completed.

An e-gift card was chosen as the compensation method due to the remote nature of participant interactions. The US $25 per survey completion amount is based on feedback from the CAB, which deemed this amount appropriate for the study’s context.

### Safety Planning and Response Protocol

We have developed a comprehensive safety plan for participants disclosing significant distress or suicidality, specifically tailored to the needs of our study population. The safety plan outlines clear procedures for monitoring, assessing, and responding to participant distress or suicidality. It was created in consultation with multiple psychiatrists and based on established safety protocols that have been successfully implemented in other studies involving mental health assessments and potential disclosures of suicidality in at-risk populations.

A detailed safety response protocol is provided to participants during the consent process and reiterated at every survey. Participants are required to complete a comprehension quiz during the consenting process to verify their understanding of the safety protocol and response procedures. They are informed that survey submissions will not be monitored in real time and are encouraged to take immediate action if they are experiencing an emergency.

All surveys that intentionally assess suicidality, self-harm, and depression-related survey results are reviewed within a 24-hour window by the research team. Crisis management procedures and clinical assessments, as outlined in the safety protocol, are conducted by a board-certified psychiatrist using appropriate clinical interventions. If a participant’s responses indicate significant distress or suicidality, a board-certified psychiatrist conducts a clinical assessment to determine the appropriate course of action.

Personalized referral information is provided to participants based on their assessment results and clinical recommendations. Participants identified as at risk for harm to themselves or others are referred to appropriate mental health services, including emergency departments or crisis hotlines. The research team does not discourage participants from seeking or continuing mental health care or treatments during the study. Participants are explicitly informed, both during recruitment and throughout the study, that their voluntary participation in the research is not a substitute for other mental health interventions.

### Ethical Considerations

Boston Children’s Hospital (BCH) is the prime grant awardee and serves as the primary site for study operations and implementation. The BCH Institutional Review Board (IRB) serves as the single IRB of record for the study (protocol approval number IRB-P00046532).

The University of Michigan School of Public Health, which houses the methodology and data analysis core, and Massachusetts General Hospital, which serves as the clinical psychiatry and mental health safety core, are designated as relying sites under the single IRB structure. The study is covered by a Certificate of Confidentiality from NIH.

A data safety and monitoring board has been established to oversee the trial’s progress, review safety data, and make recommendations regarding the continuation of the trial based on its evaluation of participant safety and the overall performance of the research.

### Statistical Analysis

#### Power

The study aims to enroll 500 TGD participants between the ages of 18 and 24 years, 125 caregivers, and one-quarter of the young adult sample in a TGD young adult-caregiver dyad. The primary outcome of interest is past 3-month suicidal ideation.

Power calculations determined the sample size needed to detect a significant difference in suicidal ideation between the immediate and deferred intervention arms. To detect an effect size of at least 30% (risk ratio=0.70) in the reduction of suicidal ideation from baseline to 6 months postrandomization, a total sample size of 400 participants (200 per arm) is required to achieve 80% power at a 0.05 significance level.

We selected a 30% effect size threshold based on the assumption that smaller differences would not be clinically meaningful for public health scale-up. To account for an estimated 20% attrition rate, we plan to enroll 500 TGD young adult participants and 125 caregivers at baseline, yielding an anticipated analyzable sample of 400 TGD young adult participants and 100 caregivers.

#### Primary Aim Analyses

The primary outcome is suicidal ideation in the past 3 months, assessed using the 6-item C-SSRS. The C-SSRS demonstrates strong validity, with 100% sensitivity and 99.4% specificity for identifying aborted suicide attempts, and 100% sensitivity and specificity for classifying interrupted and actual suicide attempts, when compared to clinician-administered instruments [41]. The secondary outcome is depressive distress over the past 2 weeks, measured using the Patient Health Questionnaire-9, where a score of ≥10 indicates a positive screen for symptoms of clinically elevated depressive symptoms (88% sensitivity and 88% specificity for detecting major depression) [43].

Before analysis, data will be audited for quality and completeness. Descriptive statistics—including counts, percentages, means, medians, standard deviations, and ranges—will summarize baseline characteristics. Group differences at baseline will be assessed using *t* tests for continuous variables and chi-square tests for categorical variables. Variables that differ significantly between study arms may be included as covariates in subsequent models. All analyses will be conducted using SAS or R statistical software.

To evaluate intervention effectiveness, we will use an intention-to-treat approach. Poisson generalized estimating equations with a log link function will estimate the population-average (marginal) effect of the intervention on suicidal ideation from baseline to 6 months postrandomization [60]. An unstructured correlation structure will be used to account for within-subject correlations across repeated measures (baseline, 3 months, and 6 months).

The primary endpoint analysis will compare the proportion of participants reporting suicidal ideation in the past 3 months between the immediate and deferred (waitlist control) arms. The model will include a common intercept and fixed effects for the intervention arm (immediate vs deferred) and time point (3 vs 6 months). Baseline characteristics that differ significantly between groups and variables related to missingness will be included as covariates, if appropriate.

The primary estimate is the intervention arm assignment. The risk ratio will be estimated by exponentiating the intervention coefficient from the model. Wald tests with robust standard errors will be used to construct 95% CIs and test the primary hypothesis. For TGD young adult-caregiver dyads, we will adjust models to account for dyadic interdependence.

The same analytic approach will be applied to the secondary outcome of past 2-week depressive distress. Statistical significance will be determined at the 0.05 level.

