### Intervention Allocation and Randomization

Randomization occurs following completion of the enrollment visit. Participants are randomized in a 1:1 ratio to either the immediate intervention arm or the deferred arm (6-month waitlist control). TGD young adults and their caregivers who enroll as dyads are randomized together as a unit to maintain the dyadic structure of the intervention.

Randomization is conducted using an automated, computer-generated sequence within REDCap. The allocation sequence is concealed, and blinding is maintained at the analyst and investigator levels to reduce bias. Once randomization is complete, study staff notify participants of their group assignment using the participant’s preferred method of contact (eg, email or phone).

Regardless of assignment, all participants receive a curated list of national and state mental health support resources.

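### The primary GEE lists baseline as a repeated outcome but has one arm main effect, so if baseline rows enter the model the primary risk ratio is diluted toward 1

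*Protocol article*

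**What the plan says.** All statements are in the Protocol article, under Statistical Analysis.

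- **Outcome times.** Primary Aim Analyses: "An unstructured correlation structure will be used to account for within-subject correlations across repeated measures (baseline, 3 months, and 6 months").
- **Model terms.** Same section: "The model will include a common intercept and fixed effects for the intervention arm (immediate vs deferred) and time point (3 vs 6 months"). No arm-by-time term is listed, and the time factor has no baseline level.
- **Primary estimate.** Same section: "The risk ratio will be estimated by exponentiating the intervention coefficient from the model".
- **Covariates.** Baseline characteristics enter if they differ significantly between arms, and variables related to missingness may also enter. Baseline suicidal ideation is not prespecified as a covariate.
- **Powered effect.** Power: "To detect an effect size of at least 30% (risk ratio=0.70) in the reduction of suicidal ideation from baseline to 6 months postrandomization". The same section says that "a total sample size of 400 participants (200 per arm) is required to achieve 80% power at a 0.05 significance level" and treats smaller effects as not clinically meaningful.

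The visit schedule is also unsettled. Study Design and Self-Reported Surveys place surveys at baseline, 6 and 12 months. Remuneration, Primary Aim Analyses and Secondary Aims Analysis all assume a month-3 assessment.

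**The concern.** A main-effect arm coefficient is one number shared by every visit in the outcome vector. If one of those visits precedes randomization, the coefficient is partly an estimate of a ratio known in advance to be 1, and it cannot equal the post-randomization effect unless there is no effect.

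The stake is the headline result. A true 30% reduction could be reported as a reduction of under 20%, below the trial's own threshold for a meaningful effect, with less than the planned chance of significance. If baseline is instead left out, a different question stays open: whether the primary estimate is a 3/6-month average or the 6-month effect.

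**Working it through.** **Inputs.** From Power: risk ratio 0.70, 200 per arm analysed, 80% power, alpha 0.05 (two-sided assumed, since 95% CIs are planned). From Intervention Allocation and Randomization: 1:1 allocation. Not given in the article: the control-arm risk of ideation, the within-person correlation and the month-3 effect. These are assumptions below.

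**Step 1. The plan's own figure.** Without a control risk, 200 per arm cannot be reproduced directly, but it can be back-solved. With control risk p1 = 0.453, p2 = 0.70 × 0.453 = 0.317 and mean 0.385:

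n per arm = [1.96·√(2·0.385·0.615) + 0.842·√(0.453·0.547 + 0.317·0.683)]² / (0.136)² ≈ 200.

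At control risks of 30, 35, 40, 45 and 50% the same formula gives 367, 297, 244, 203 and 170 per arm. A control risk near 45% is therefore what the stated size implies, and it is used below. The attrition step reproduces: 400/0.80 = 500.

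**Step 2. Hand calculation with baseline rows as outcomes.** The model is log(risk) = intercept + β·arm + time. With complete data and working independence, the Poisson estimating equations match the fitted to the observed total in each arm, so exp(β) is the ratio of arm totals. With a flat control risk p:

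exp(β) = p(1 + 0.70 + 0.70) / 3p = 0.80.

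The control risk cancels, so the dilution does not depend on the assumed 45%.

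**Step 3. Hand calculation with post-baseline rows only.**

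- Constant effect: (0.70 + 0.70)/2 = 0.70.
- Effect that builds, for illustration a month-3 risk ratio of 0.85: (0.85 + 0.70)/2 = 0.775.

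**Step 4. Simulation.** Poisson GEE, unstructured correlation, robust Wald test, 200 per arm, control risk 45.3%, 2000 replicates. True risk ratio 0.70 at both months 3 and 6. Cells show mean estimated risk ratio and power.

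| Model | corr. 0.3 | corr. 0.6 | corr. 0.8 |
|---|---|---|---|
| Baseline+3+6, one arm main effect | 0.81, 75% | 0.81, 60% | 0.83, 47% |
| 3+6 only, one arm main effect | 0.70, 95% | 0.70, 91% | 0.70, 88% |
| Month 6 only, no baseline adjustment | 0.70, 79% | 0.70, 79% | 0.70, 80% |
| Constrained baseline, month-6 contrast | 0.70, 81% | 0.70, 86% | 0.70, 93% |
| Constrained baseline, one post-baseline arm term | 0.70, 96% | 0.70, 97% | 0.70, 98% |

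The first row is the repeated-measures sentence taken literally; the second is the time coding taken literally. At correlation 0.8, the first-row model gives 0.82 at control risks of 35, 43 and 50% alike.

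**Step 5. If the effect builds** (month-3 risk ratio 0.85, month-6 risk ratio 0.70), the 3+6 arm coefficient averages 0.78, with power of 64-77%. The constrained-baseline month-6 contrast still recovers 0.70, with power of 81-93%.

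**The case against.** The strongest reply is that the sentence defining the model gives time two levels, 3 and 6 months. A baseline row has no level in that factor, so the fitted model may be post-baseline only. On that reading with a constant effect, the estimate is unbiased and power is 88-95%, better than planned. This stands, and it is why the dilution has to be stated conditionally.

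A second reply is that pooling months 3 and 6 is a legitimate target. The outcome is ideation in the past 3 months, so the two recall windows together cover the randomized period, which fits the stated effect from baseline to 6 months. This also stands. A 3/6-month average is not an error, but it has to be declared. The month-3 risk ratio of 0.85 is only an illustration; nothing in the article supports that value or a constant effect.

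A third reply is that a common intercept means a common baseline mean, with arm acting only after baseline. That would remove the dilution, but it needs a baseline level of time and a post-baseline arm term, and neither is listed. Supplemental Analyses uses the same phrase for a model fitted in the immediate arm alone, where it can only mean an intercept.

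A reader might infer that the trial will report a true 30% reduction as 14-19% whatever happens. The documents do not support that. The 19% end requires baseline rows to be outcomes. The 14% end also requires that no month-3 survey exists, which belongs to the separate schedule conflict. Nor is type I error inflated: with no effect, the expected ratio is 1 at every visit. Leaving baseline ideation out of a post-baseline model costs precision and does not bias the estimate, and ideation could still enter through the missingness route.

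**Conclusion.** The point holds in conditional form. The primary model's stated outcome times and stated terms disagree, and following the repeated-measures sentence literally gives a diluted primary estimate: 0.80 by hand and 0.81-0.83 by simulation for a true 0.70, with power of 47-75% against the planned 80%. The direction follows from randomization alone. The size rests on an assumed 45% control risk (which matters for power, hardly for the ratio), a flat control risk, correlation of 0.3-0.8 and a constant effect from month 3.

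Under the post-baseline reading there is no dilution. What remains is an undeclared choice between a 3/6-month average and the month-6 effect, and use of baseline ideation that depends on a significance test or on missingness. Because this is the primary estimate, the wording should be settled before analysis.

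**What to change.** 1. Remove baseline from the outcome rows. Fit the log-link GEE to post-baseline visits with baseline suicidal ideation as a prespecified covariate, whether or not it differs between arms. Alternatively, keep all visits in a constrained-baseline model in which arm acts only after baseline.
2. Name the primary contrast: either the month-6 risk ratio through an arm-by-time term, or an explicitly declared 3/6-month average.
3. Match the Power section to that contrast and state the control risk behind 200 per arm.
4. Reconcile the month-3 survey across Study Design, Self-Reported Surveys, Remuneration, Primary Aim Analyses and Secondary Aims Analysis. If it does not exist, the time factor and the averaging option both fall away.

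The cost is protocol and SAP wording; baseline ideation is already collected. Choosing month 6 gives up some precision if the effect is constant: 81-93% power against 96-98% for one post-baseline arm term, both with a constrained baseline. Compared with an unadjusted 3/6-month average (88-95% in Step 4), the loss is smaller. If the effect builds over time, the month-6 choice protects the effect that the trial says it was powered for.

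### The primary model picks covariates by baseline significance tests and leaves the role of baseline suicidal ideation unclear; it should be prespecified instead

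*Protocol article*

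**What the plan says.** Primary Aim Analyses plans t tests and chi-square tests between arms at baseline, and then uses the results twice. The paragraph on data preparation is permissive: "Variables that differ significantly between study arms may be included as covariates in subsequent models". The paragraph on the primary endpoint is firmer but hedged: "Baseline characteristics that differ significantly between groups and variables related to missingness will be included as covariates, if appropriate".

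The terms named for the primary Poisson GEE are a common intercept, arm, and time point with the two levels month 3 and month 6. Baseline suicidal ideation is not named as a covariate. The preceding paragraph, however, counts baseline with months 3 and 6 among the repeated measures covered by the unstructured correlation, and describes the effect as running from baseline to month 6.

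On size, the Power section takes a risk ratio of 0.70 at month 6 as its target and concludes for it: "a total sample size of 400 participants (200 per arm) is required to achieve 80% power at a 0.05 significance level". It gives no control-arm risk and no correlation between baseline and follow-up ideation.

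**The concern.** Assignment is random, so a significant baseline difference is a chance event. It says nothing about whether the variable predicts the outcome. A rule keyed to that p-value can admit irrelevant variables and pass over a strong predictor that happens to be balanced. The primary model is then known only after the arms have been compared, and the two sentences differ on whether a flagged variable must enter.

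The variable most likely to matter is baseline ideation: the same measure as the outcome, collected on everyone at enrolment. The stated terms leave three readings open: baseline ideation is unused unless flagged; it is an outcome row with the arms constrained equal at baseline; or it is an outcome row with arm as a plain main effect. These differ in power, and the third also differs in what the arm coefficient estimates.

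**Working it through.** **Inputs from the protocol article.** Risk ratio 0.70; 200 analysed per arm; 80% power; alpha 0.05 ("Statistical significance will be determined at the 0.05 level"; taken as two-sided, in line with the 95% CIs); 1:1 allocation; 20% attrition.

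**Assumed, because not stated.** Control-arm risk, and baseline-to-follow-up correlation rho from 0.3 to 0.6.

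**Step 1: the plan's own figure.** Attrition reproduces: 400 / (1 − 0.20) = 500. The figure of 200 per arm can only be back-solved. With a pooled two-sided comparison of proportions:

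| Control risk | Needed per arm | Power at 200 per arm |
|---|---|---|
| 0.30 | 367 | 54.2% |
| 0.40 | 244 | 71.8% |
| 0.45 | 203 | 79.6% |
| 0.46 | 196 | 81.0% |
| 0.50 | 170 | 86.1% |

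So the plan is consistent with a control risk of about 0.45 to 0.46, which is used below as an assumption.

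**Step 2: month-6 gain from always adjusting for baseline ideation.** Adjustment multiplies the variance by about 1 − rho², so from 80% power:

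power = Φ[(1.960 + 0.842) / √(1 − rho²) − 1.960]

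For rho = 0.5: 2.802 / 0.866 = 3.235; 3.235 − 1.960 = 1.275; Φ = 89.9%. The last column is 400 × (1 − rho²).

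| rho | Power by formula | Gain (points) | Simulated gain, control risk 0.45 | N giving 80% if adjusted |
|---|---|---|---|---|
| 0.3 | 83.6% | 3.6 | 2.8 | 364 |
| 0.4 | 86.4% | 6.4 | 5.6 | 336 |
| 0.5 | 89.9% | 9.9 | 8.2 | 300 |
| 0.6 | 93.8% | 13.8 | 12.2 | 256 |

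The simulations used modified Poisson models with robust standard errors, 4,000 runs each. If control risk runs from 0.30 to 0.50, so that power does not start at 80%, the formula gives gains of 3 to 19 points.

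**Step 3: does the significance rule recover the gain?** Hardly. At control risk 0.45 and rho 0.5, simulated power was 78.1% unadjusted, 79.1% when baseline ideation entered only if its baseline test was significant, and 86.3% when it always entered. Across all settings the rule stayed within about 1.5 points of no adjustment. Its type I error was 3.6% to 5.1%, so not inflated.

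**Step 4: the readings of the GEE.** Poisson GEE, unstructured correlation, true risk ratio 0.70 at months 3 and 6, control risk 0.45, rho 0.5, 200 per arm, 1,500 runs:

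| Use of baseline ideation | Mean RR | Power |
|---|---|---|
| Not used; outcomes at months 3 and 6 | 0.70 | 89.1% |
| Covariate; outcomes at months 3 and 6 | 0.70 | 97.1% |
| Outcome row, arms constrained equal at baseline | 0.70 | 96.9% |
| Outcome row, arm as plain main effect | 0.82 | 52.1% |

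In the last row, the arm coefficient averages over a visit at which no effect can exist. With rho 0.4 or 0.6 the risk ratio under that reading was 0.81 or 0.82.

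**The case against.** The strongest reply is that baseline ideation may already be in the model. It is listed among the repeated measures, and a common intercept could mean that the arms share one baseline level. Under that constrained-baseline reading, power matches covariate adjustment (96.9% against 97.1%) and almost nothing is lost. This stands as a possibility, and it rules out asserting that baseline ideation enters only when its test is significant, which a reader might infer. But the text does not describe that model: time has no baseline level, and no term confines the arm effect to follow-up visits. Supplemental Analyses also uses the common-intercept phrase for a model of the immediate arm alone, where no between-arm constraint is possible.

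A second reply is that the power loss rests on assumptions. That is correct. A reader might put it at 7 to 15 points, but that needs rho of about 0.42 to 0.63 and a start at 80%; at rho 0.3 it is 3 to 4 points. The month-6 comparison is also not the planned two-visit GEE, where power without baseline was already 89.1% in the setting above.

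A third reply is that analysts are blinded and a separate analysis plan may fix the list. Blinding lowers the risk of bias, but it does not specify the model. Nor is this a missing detail: the article states a covariate rule for the primary analysis, and the rule is poor.

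Finally, predictors of missingness in the outcome model are a legitimate way to handle covariate-dependent dropout, and Attrition Analysis separately plans multiple imputation. Their inclusion is no fault. Leaving their choice to the data is.

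**Conclusion.** The concern holds in a limited form. The covariate rule selects on chance imbalance rather than prognosis and leaves the primary model undetermined until the arms are compared. The role of baseline ideation is ambiguous, and the consequences range from nearly nothing (constrained baseline), through about 3 to 14 points of month-6 power (baseline unused, rho 0.3 to 0.6, planned power 80%), to a diluted risk ratio of about 0.82 in place of 0.70 (baseline row with a plain arm effect). The figures rest on an assumed correlation and, for the simulations, mainly on a back-solved control risk of 0.45.

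A reader might also infer that the rule inflates false positives. The simulations of selection on baseline ideation do not show that. They did not examine selection over many covariates at once, so the objection there is to the lack of prespecification, not to a demonstrated error rate.

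**What to change.** - Delete baseline significance testing as a covariate rule in both sentences of Primary Aim Analyses, and keep the baseline table descriptive.
- Prespecify baseline past 3-month suicidal ideation in the primary model whatever the observed balance, in one of two stated forms: as a covariate with only post-randomization visits as outcomes; or as a baseline outcome with the arms explicitly constrained equal, a time term that includes baseline, and the arm effect confined to follow-up.
- Do the same with baseline PHQ-9 in the depressive distress model.
- Fix any further covariates, including predictors of missingness, before unblinding.
- While editing, reconcile the visits. The model uses month 3, and Remuneration pays for a 3-month survey, but Study Design and Self-Reported Surveys list only baseline, 6 and 12 months.

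The cost is negligible: the wording changes and the baseline data are already collected. With a log link, and absent effect modification by baseline ideation on the ratio scale, adjustment still targets the marginal risk ratio that the plan intends.
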